#### Intervention (LWL group)

Participants allocated to the intervention study arm will be provided immediate access to the LWL program via their participant portal. The active study period for completion of the intervention is 8 weeks, with participants encouraged to login and review a module each week via automated email reminders. As the LWL program is being evaluated as a self-guided low-intensity intervention, no telephone or email therapist support or coaching for program content will be provided (e.g., around use of strategies). Participants will receive email notifications and reminders to login to their participant portal and complete the relevant study questionnaires when available. Once all three assessment timepoints have been completed, participants will have completed their participation in this trial. Participants in the intervention arm (LWL group) will be invited to complete a 6-month follow-up assessment following completion of the LWL program.

#### Control (CAU group)

Participants allocated to the control study arm will be notified on the homepage of their participant portal that they have completed the first stage of the research study (timepoint 1; baseline questionnaires), with two further stages to be completed in 8 weeks’ time (timepoint 2); and 3 months’ time (timepoint 3). Participants will receive email notifications and reminders to login to their participant portal and complete the relevant study questionnaires when available. Once all three assessment timepoints have been completed, participants in the control arm will have completed their participation in this trial and will be provided the option to access the LWL program through their participant portal.

#### Safety monitoring

Two primary strategies are in place to monitor participants and ensure their safety throughout the trial. Participant progress will be monitored by the trial clinician to identify elevated distress or risk of harm. The trial clinician [name] is a registered psychologist in Australia with clinical experience in managing perinatal mental health difficulties and diagnoses. Both the participant and the trial clinician will receive automated notification emails if severe symptoms of distress (i.e., total score ≥30 on the K10), depression (i.e., total score ≥13 on the EPDS), or thoughts of self-harm (i.e., item 10 on the EPDS, item 8 on the Perinatal Grief Scale-Short Form (PGS-SF) [43], or item 16 on the Assessment of Quality of Life (AQoL-8D) [44] are indicated at any of the primary timepoints. This notification email will encourage participants to seek support from their support network (e.g., partner, family member) and health professional (e.g., GP/Family Doctor), and if feeling unsafe, to contact emergency or crisis support services. Participants will be contacted by the trial clinician within 72 h via telephone to conduct a risk assessment and determine whether the participant is still eligible to continue in the study, and will be provided assistance to find appropriate support and clinical care if required.

### Outcomes

Primary and secondary outcomes will be collected at three primary timepoints: baseline, post-intervention, and 3-month follow-up (see Table 2).

**Table 2 Tab2:** Schedule of outcome measures and timepoints

	Baseline	Active study period^a^		Post-intervention	3-month follow-up
		Weekly	End of each module		
***Primary outcome***					
K10	x*	x		x	x
***Secondary outcomes***					
PGS	x			x	x
GAD-7	x			x	x
EPDS	x*			x	x
BGQ	x				
RSA	x				
DRS	x			x	x
Support use	x			x	x
AQoL-8D	x			x	x
HSUS	x			x	x
***Acceptability outcomes***^a^					
CEQ			x^b^		
MSS			x		
PSQ				x	

*K10* Kessler Psychological Distress Scale, *PGS* Perinatal Grief Scale, *GAD-7* Generalized Anxiety Disorder Scale, *EPDS* Edinburgh Postnatal Depression Scale, *BGQ* Brief Grief Questionnaire, *RSA* Resilience Scale for Adults, *DRS* Decisional Regret Scale, *CEQ* Credibility and Expectancy Questionnaire, *MS* Module Satisfaction Scale, *PSQ* Program Satisfaction Questionnaire, *AQoL-8D* Assessment of Quality of Life, *HSUS* Health Service Utilization Scale

*Completed during enrolment screening questionnaire; ^a^LWL group only; ^b^end of Module 1 only

#### Primary outcome—psychological distress

The Kessler Psychological Distress 10-item scale (K10) [40]—a self-report scale to assess symptoms over the past 4 weeks. Items are rated on a 5-point scale from 1 (none of the time) to 5 (all of the time). In addition to the three primary timepoints, participants in the LWL group will also complete the K10 once per week while completing the intervention to monitor for potential harmful effects of the intervention such as symptom deterioration [45]. The K10 has strong psychometric properties, is sensitive to change (i.e., in tracking symptom changes in response to treatment [46]), and has been used in efficacy studies of digital mental health interventions including perinatal populations [21, 22] and in the context of grief [47, 48].

#### Secondary outcomes

*Perinatal Grief Scale – Short Form* (PGS-SF) [45] is a 33-item self-report measure of behavioral and affective symptoms of grief and symptoms specific to perinatal loss. Statements of thoughts and feelings are divided into three subscales: “active grief,” “difficulty coping,” and “despair” and are rated on a 5-point scale from 1 (strongly agree) to 5 (strongly disagree). Higher scores are reflective of more intense grief. The PGS-SF has been widely used and translated into multiple languages [49].*Generalized Anxiety Disorder Scale, 7-Item* (GAD-7) [50] is a self-report measure to assess generalized anxiety symptoms over the past 2 weeks and is sensitive to the presence of generalized anxiety disorder, social phobia, panic disorder, and posttraumatic stress disorder [51]. Participants are asked to rate on a 4-point scale from 0 (not at all) to 3 (nearly every day) whether they have been bothered by anxiety symptoms including nervousness, inability to stop worrying, excessive worry, restlessness, difficulty relaxing, irritation, and feeling afraid. Total scores range from 0 to 21, with higher scores indicating more severe anxiety symptoms. A total score of 8 or more indicates the likely presence of an anxiety disorder.*Edinburgh Postnatal Depression Scale* (EPDS) [41] is a 10-item self-report screening measure to assess antenatal and postpartum depressive symptoms over the past 7 days. Items are rated on a 4-point scale from 0 (not at all) to 3 (most of the time). Total scores range from 0 to 33, with a score of 12 or greater indicating possible depression. The EPDS has strong psychometric properties, has been validated in women and men [52], and translated and validated in 20 languages [53].*Brief Grief Questionnaire* (BGQ) [54] is a 5-item self-report measure for screening complicated grief symptoms, including difficulty accepting the death, grief interference in current life, troubling thoughts related to the death, avoidance of reminders of the loss, and feeling distant from others. Items are rated on a 3-point scale from 0 (not a lot) to 2 (a lot) with a total score of five or more indicating the presence of complicated grief symptomology [55].*Decisional Regret Scale* (DRS) [56] is a 5-item self-report measure assessing the extent of distress or remorse after a health care decision. Items are answered on a 5-point scale from 1 (strongly agree) to 5 (strongly disagree). Total scores range from 0 to 100, with higher scores indicating high regret [56].*Resilience Scale* (RS-14) [57] is a 14-item self-report measure of personal resilience, defined by the individual’s capacity to cope with stress and thrive despite life challenges. Responses are scored on a 7-point scale from 1 (strongly disagree) to 7 (strongly agree). Scores range from 14 to 70, with higher scores indicating greater resilience. The RS-14 has been validated in bereaved parent populations [34].*Use of other supports and/or treatments*: At each primary timepoint, participants will be asked to provide details of other support services they have accessed before and during the trial period including both informal (e.g., family, friends, spiritual advisor) and formal supports (e.g., mental health professional, parent support organizations).

#### Health economic outcomes

##### Quality of life and health service utilization

Quality of life will be assessed according to the Assessment of Quality of Life (AQoL-8D) [44], a 35-item self-report scale to assess health-related quality of life across eight dimensions: independent living, pain, senses, mental health, happiness, coping, relationships, and self-worth. Health service utilization will be assessed using a 23-item self-report questionnaire developed for this trial to explore health service utilization of nine services: general practitioners/nurse practitioners, psychology services, specialist services, hospital emergency department services, hospital inpatient services, hospital outpatient services, medications, other services; and out-of-pocket service fees incurred.

#### Acceptability outcomes—LWL group only

##### Expectancy of benefit

Credibility and expectancy of benefit will be assessed after completion of the first module. Two questions assess expectations around the usefulness and benefit of the LWL program (e.g., “How useful do you think the information or modules of the LWL program will be?”) and one question assesses concerns about the program (e.g., “Do you have any concerns about the program?”) with all responses rated on a 5-point scale from “very useful” to “not useful”. An open-ended question invites any further comments.

##### Engagement with LWL program

Adherence to the program will be reflected in the mean number of sessions completed by participants. Other website analytic tools will allow program usage (e.g., number of times logged in, number of times a module has been accessed and completed, time spent per module, and order modules were completed) to be assessed.

##### Program satisfaction and experiences

Participants are asked to provide feedback on the program: (1) immediately after completing a module and (2) at post-intervention. At the end of each module, participants are asked to rate five statements on a 5-point scale (from strongly agree to strongly disagree) which assess the perceived helpfulness and usefulness of each module’s topics, themes, activities and strategies, and ease of use. Participants are also asked to provide descriptive feedback around aspects of the module that they did not find helpful, aspects which they felt were missing, and to provide suggestions for revisions and improvements. Following completion of the program (and end of active trial period), participants are asked 12 questions around their overall experience which include a range of open-ended, brief rating scales, and multiple-choice responses. Questions assess the perceived helpfulness of program content (e.g., character stories, strategies, activities) and ease of use, feedback on desired involvement of healthcare professionals for additional support (e.g., weekly check-ins, telephone support), and how likely the participant would be to recommend the LWL program to their GP or other bereaved parent. These questionnaires were developed specifically for this trial and are based on similar intervention satisfaction measures (i.e., the *Treatment Satisfaction Questionnaire* (TSQ) [58].

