The *NHMRC Centre of Research Excellence in Stillbirth* (Stillbirth CRE) have led the development of a parent-centered internet-based program to improve the emotional wellbeing of parents following stillbirth or neonatal death and expand the availability and accessibility of evidence-based bereavement care options in Australia for parents and healthcare professionals. The aim of this trial is to conduct a RCT to evaluate the efficacy and acceptability of the internet-based Living with Loss (LWL) perinatal bereavement program, compared to standard usual care. We hypothesize that the LWL program will:Reduce symptoms of psychological distress compared with usual care.Reduce grief intensity, anxiety, depression, decisional regret, and improve quality of life outcomes compared to usual care.Be perceived as helpful, with participants reporting high levels of program satisfaction including usability, credibility and quality; and low attrition rates.Be cost-effective compared with usual care.

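### The end-of-program satisfaction questionnaire has two different triggers, one of which would limit it to parents who finish, and the concerns item has a response scale that cannot express concern

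*Protocol article*

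**What the plan says.** Acceptability is part of the stated aim. The third hypothesis in the Background is that the program will "Be perceived as helpful, with participants reporting high levels of program satisfaction including usability, credibility and quality; and low attrition rates".

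The ratings are collected in the LWL arm only, at these points:

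- **Program satisfaction (PSQ), text.** Program satisfaction and experiences says: "Following completion of the program (and end of active trial period), participants are asked 12 questions around their overall experience".
- **Program satisfaction, same paragraph and Table 2.** The paragraph opens with: "Participants are asked to provide feedback on the program: (1) immediately after completing a module and (2) at post-intervention". Table 2 marks the PSQ in the post-intervention column without a completion footnote. The active period is set by the calendar: "The active study period for completion of the intervention is 8 weeks".
- **Module satisfaction.** "At the end of each module, participants are asked to rate five statements on a 5-point scale".
- **Credibility and expectancy.** "Credibility and expectancy of benefit will be assessed after completion of the first module". The Table 2 footnotes agree: "Completed during enrolment screening questionnaire; ^a^LWL group only; ^b^end of Module 1 only". Two questions cover usefulness and benefit and one covers concerns. All are answered on five points from very useful to not useful, and an open comment follows.

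Engagement with LWL program adds automatic usage data, such as logins and modules accessed and completed. Randomization and allocation procedures states that those who withdraw or drop out give no further outcome data. Data analyses provides descriptive summaries for engagement, adherence and satisfaction.

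**The concern.** The program is self-guided, and after the introductory module parents choose their own order and pace, so many may reach week 8 without having finished. Whether they are asked for an overall rating depends on which trigger is built into the course system. One trigger gives satisfaction among finishers. The other gives satisfaction among everyone still in the trial at week 8. These are different quantities, and only the second comes close to describing acceptability in the arm as randomised.

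The other ratings do not fully close the gap. A module abandoned midway is not rated, because that form comes "immediately after completing a module". A parent who stops inside Module 1 has no expectancy value. Usage logs show that someone stopped, but not whether the reason was dissatisfaction, lack of time or feeling better. A rating that was never requested cannot be recovered by any later analysis plan.

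The concerns item is a separate fault. A parent with serious concerns and a parent with none have no meaningful way to differ on a scale of usefulness.

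**Working it through.** The protocol gives no figure for acceptability, so there is none to reproduce. The check sets the passages side by side and then illustrates the possible size.

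**1. Who is asked, by situation of an LWL parent**

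| Parent | Module rating | Expectancy | PSQ, completion trigger | PSQ, post-intervention trigger |
|---|---|---|---|---|
| Finishes all modules, stays in trial | yes | yes | asked | asked |
| Stops after Module 1 or later, stays in trial | for modules completed | yes | not asked | asked |
| Stops during Module 1 with no other module finished, stays in trial | no | no | not asked | asked |
| Stops after Module 1 or later, drops out before week 8 | for modules completed | yes | not asked | not asked |
| Stops during Module 1, drops out before week 8 | no | no | not asked | not asked |

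The triggers differ in the second and third rows: parents who stop the modules but remain in the trial. No completion rate is given, so the size of this group is unknown.

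**2. Illustration of size**

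Inputs from the protocol: at least 75 per arm (Participants and recruitment) and 25% anticipated dropout (Sample size calculation). At that rate 75 × 0.25 = 18.75, about 19 LWL parents, would give no program rating, and 75 × 0.75 = 56.25, about 56, could.

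Assumed: 80% of raters are satisfied, and satisfaction among non-raters lies between 0% and 80%.

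Formula: overstatement = share not rating × (satisfied among raters − satisfied among non-raters).

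With 25% not rating:

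| Non-raters satisfied | Share in whole arm | Overstatement |
|---|---|---|
| 0% | 0.75 × 80 + 0.25 × 0 = 60% | 20 points |
| 20% | 0.75 × 80 + 0.25 × 20 = 65% | 15 points |
| 40% | 0.75 × 80 + 0.25 × 40 = 70% | 10 points |
| 60% | 0.75 × 80 + 0.25 × 60 = 75% | 5 points |
| 80% | 0.75 × 80 + 0.25 × 80 = 80% | 0 points |

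Over the same range, 10% not rating gives 0 to 8 points (0.10 × 80 = 8), and 50% not rating gives 0 to 40 points (0.50 × 80 = 40).

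**3. What the illustration does and does not show**

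The 25% is borrowed from the dropout assumption. Dropouts are missed under either trigger. The completion trigger adds parents who stay in the trial but do not finish, so the share not rating rises above dropout alone. If it rose from 25% to 50%, the upper end would move from 20 to 40 points. If non-raters were more satisfied than raters, the sign would reverse: with all of them satisfied, 0.25 × (80 − 100) = −5 points.

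**The case against.** The strongest reply is that the post-intervention timing is the natural reading. The paragraph's opening sentence and Table 2 agree on it, the active period is a fixed 8 weeks, the longer sentence itself mentions the end of that period, and questionnaire reminders are not tied to module completion. On that reading most of the fix is already planned. This is a fair account of probable intent. It does not remove the literal wording, which makes program completion a condition for the main satisfaction measure.

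A reader might go further and infer that every acceptability measure depends on completion, that parents who stop never rate the program, and that the third hypothesis is tested only on satisfied finishers. The documents do not support this:

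- The PSQ is also scheduled at post-intervention without a completion condition.
- Parents who stop after a module have already rated it and commented on what did not help. Those who completed Module 1 have also given expectancy ratings.
- The hypothesis includes attrition, and usage data are recorded without any rating.
- The summaries are descriptive, so nothing is formally tested.
- An upward bias presumes that non-raters are less satisfied. That is plausible but not shown.

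It can also be said that denominators belong to an analysis plan, and that an article may condense its instruments. Both are reasonable. The reporting advice below accompanies the fix and is not a charge of omission. The concerns item is judged as printed, and the open comment softens the fault without making the rating interpretable.

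Asking expectancy after Module 1 mixes it with experience. But the measure also covers credibility, five modules remain, and the timing is explicit, so this is a trade-off and not an error.

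**Conclusion.** The point holds as an inconsistency in the release rule for the main acceptability instrument, together with one mismatched response scale. If the completion trigger is followed, overall satisfaction describes finishers only and would probably be overstated. The amount cannot be determined from the documents. The 0 to 20 point range rests on 25% not rating, 80% of raters satisfied, and non-raters no more satisfied than raters. Even with the post-intervention trigger, dropouts remain unrated. Module ratings and expectancy still need a completed module, and no item described asks why a parent stopped, so the logs count those who stop without recording their opinion. The primary K10 comparison is not affected.

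**What to change.** - In Program satisfaction and experiences, state that the PSQ is released at week 8 (post-intervention) to every participant randomised to LWL who has not withdrawn, whatever number of modules was completed. Confirm that the course system does this.
- Add one PSQ item on the main reason for not finishing.
- Report satisfaction with the number rating out of all randomised to LWL, and by number of modules completed.
- Give the concerns item a response scale that fits it.

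Moving expectancy to before Module 1 is optional and not part of this point.

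The cost is a check or change of one release rule, one added item, one corrected scale and a minor amendment. Non-completers will respond less often than completers, so some selection will remain, but it will be visible. Trial status reports 62 allocated, 31 of them to LWL. That leaves 150 − 62 = 88 to enrol, about 44 in LWL at 1:1. Answers already given on the old items should be reported separately from those on the new ones.

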### Data management and monitoring

This study is co-ordinated and managed by the Stillbirth CRE located at Mater Research Institute (MRI) within The University of Queensland Faculty of Medicine in Brisbane, Australia. All participation procedures and data collection will be conducted through the custom-built LWL online course delivery system managed by the coordinating research team based at the Stillbirth CRE. Re-identifiable data only (i.e., coded) will be exported weekly from the LWL course delivery system by a member of the research team and stored in accordance with Stillbirth CRE data management specifications. There is no data monitoring committee or planned interim analyses given this is a short-term small study involving a low-risk intervention. Participant safety is monitored by the trial clinician as part of the intervention. A steering group has been established to oversee and review data validity and overall conduct of the trial. This steering group includes clinicians, researchers, parent support and advocacy organizations, and bereaved parents who collectively provide specialist knowledge of design and conduct of RCTs, perinatal bereavement care and mental health, and lived experience of perinatal loss.

### Statistical methods

#### Sample size calculation

As the primary outcome in this trial is both continuous and measured longitudinally, we employed the sample size calculation suggested by Diggle and colleagues [59]. Assuming a significance level of 0.05, 80% power, a moderately strong within-subject correlation (*ρ* = 0.5), three timepoints, and an anticipated dropout rate of 25%, a minimal total sample size of 150 participants is required to detect a standardized difference (Cohen’s *d*) of 0.5 (i.e., a “moderate” difference between groups). This power calculation was informed by published RCTs of brief digital mental health interventions for posttraumatic stress and prolonged grief in parents after the loss of a child during pregnancy [29] and psychological distress, anxiety, and depression in postpartum women [22].

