**Methods:**

This trial is a two-arm parallel group randomized controlled trial comparing the intervention arm (LWL) with a care as usual control arm (CAU). We anticipate recruiting 150 women and men across Australia who have experienced a stillbirth or neonatal death in the past 2 years. Participants randomized to the LWL group will receive the six-module internet-based program over 8 weeks including automated email notifications and reminders. Baseline, post-intervention, and 3-month follow-up assessments will be conducted to assess primary and secondary outcomes for both arms. The primary outcome will be the change in Kessler Psychological Distress Scale (K10) scores from baseline to 3-month follow-up. Secondary outcomes include perinatal grief, anxiety, depression, quality of life, program satisfaction and acceptability, and cost-effectiveness. Analysis will use intention-to-treat linear mixed models to examine psychological distress symptom scores at 3-month follow-up. Subgroup analyses by severity of symptoms at baseline will be undertaken.

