### Participants and recruitment

An opportunity sample of self-selecting participants will be recruited via a snowball sampling strategy. Parents and healthcare professionals will be notified of this trial through online and social media advertising, flyers at local maternity services (e.g., Mater Mothers’ Hospital, Brisbane, Australia), and by word of mouth (e.g., healthcare professionals; parent support organizations). All parents interested in participating are directed to the LWL website to review participant information and express interest. This trial aims to recruit at least 75 participants in each study arm (total *N* = 150) which allows for an anticipated dropout rate of 25% (see Statistical methods). Participants will be recruited over a 12-month period.

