#### Data analyses

All analyses will be undertaken in Statistical Package for the Social Sciences (SPSS) version 25 (IBM SPSS, IBM Corp., Armonk, NY, USA) using re-identifiable (i.e., coded) data. Data analysts will not be blinded to study arm. Descriptive statistics will be used to summarize participant demographic and obstetric data. Group differences in baseline variables will be examined using cross-tabulations, independent *t*-tests, and regression analyses, with differences in baseline outcome measures controlled for in further analyses. To determine program efficacy, intention-to-treat linear mixed models will be estimated for each outcome measure, with restricted maximum likelihood (REML) estimation used to account for missing data due to participant dropouts [60]. These models will yield more accurate estimates of effect compared to completer as they account for the unbalanced nature of the data [60, 61]. Mixed models will be estimated separately for each outcome variable, with time, group, and time by group interaction entered as fixed factors. Comparisons within and between groups from baseline to 3-month follow-up for each group will be undertaken for outcomes. Between-group effect sizes will be calculated using the pooled standard deviation of the estimated marginal means and adjusted for sample size (Hedges *g*). Effect sizes of 0.20, 0.50, and 0.80 are considered small, moderate, and large respectively [62]. Descriptive statistics will be used to summarize participant engagement, adherence, and program satisfaction data.

A cost-utility analysis comparing the program’s efficacy and acceptability against usual care in a primary care setting will be conducted. Analyses will be based on direct and indirect costs associated with program development, evaluation, and participants’ social opportunity costs (e.g., work productivity, absenteeism, and presenteeism). The health economic evaluation protocol and findings from this trial will be published separately.

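### The stated inputs do not give 150 at 80% power, and the calculation is not tied to the primary contrast; 150 is still roughly adequate for that contrast

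*Protocol article*

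**What the plan says.** The Sample size calculation section of the protocol article cites a longitudinal method and lists its inputs. It opens with "Assuming a significance level of 0.05, 80% power", continues with "a moderately strong within-subject correlation (*ρ* = 0.5), three timepoints", and concludes, "three timepoints, and an anticipated dropout rate of 25%, a minimal total sample size of 150 participants is required", the aim being "to detect a standardized difference (Cohen’s *d*) of 0.5". It does not say whether the average-response or the slope version of the method was used, or whether the test is one- or two-sided. Participants and recruitment repeats the target: "This trial aims to recruit at least 75 participants in each study arm (total *N* = 150) which allows for an anticipated dropout rate of 25" per cent.

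The abstract defines the endpoint: "The primary outcome will be the change in Kessler Psychological Distress Scale (K10) scores from baseline to 3-month follow-up". Data analyses plans intention-to-treat linear mixed models fitted by REML, "with time, group, and time by group interaction entered as fixed factors". The same section says that groups will be compared at baseline and that differences found in baseline outcome measures will be controlled for afterwards.

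**The concern.** The article gives every numeric input and the result, so the calculation can be checked, and it fails the check. This is not detail that a condensed article leaves to a fuller document, because what is printed does not agree with itself.

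There is also a mismatch of target. An average over the three timepoints includes baseline, where randomisation leaves no treatment effect to detect. The primary outcome is a change to one later visit. Power for the first quantity says little about power for the second.

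The stake is practical. Trial status reports 62 randomised by 1 February 2022 against a target of 150. Anyone deciding whether a smaller total would do needs a power statement for the primary contrast. Someone who redoes the printed calculation may arrive at 112 and take that as enough, and for the primary contrast it is not.

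**Working it through.** **Inputs from the protocol article:** α = 0.05, power 80%, ρ = 0.5, three timepoints, 25% dropout, d = 0.5 (Sample size calculation); 1:1 allocation (Randomization and allocation procedures). **Assumptions made here:** two-sided test, compound symmetry, SD = 1 at every visit, dropout missing at random.

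Let k = (z₁₋α/₂ + z_power)². Then k = (1.960 + 0.842)² = 7.849 at 80% power and (1.960 + 1.282)² = 10.507 at 90%.

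**1. Attempt to reproduce 150**

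*Average of three timepoints:* n per arm = 2k[1 + 2ρ]/(3d²).
- At 80%: 2 × 7.849 × (2/3)/0.25 = 41.86, so 42 per arm. Total after dropout: 84/0.75 = 112. A one-sided test gives 88.
- At 90%: 2 × 10.507 × (2/3)/0.25 = 56.04. Then 56.04/0.75 = 74.7, so 75 per arm and 150 in total (152 if first rounded up to 57 per arm).

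*Slope over the trial period:* n per arm = 2k(1 − ρ)/(S d²), where S is the sum of squared deviations of the visit times with the period scaled to 1.
- Equal spacing: S = 0.5, n = 62.79, total 2 × 62.79/0.75 = 167.4 (168 rounded up).
- Weeks 0, 8 and 21: S = 0.509, n = 61.63, total 164.3 (166 with whole participants per arm).
- With dropout added as N × 1.25 instead: 157.0 and 154.1.

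None of these gives 150 at 80% power.

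**2. Power of 150 for the primary contrast**

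With 75 per arm, the variance of the between-group contrast is 2v/75, where v depends on when the 25% are lost and on whether baseline is adjusted for. Under compound symmetry with ρ = 0.5:

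*Unadjusted change from baseline to 3 months, mixed model keeping partial data*
- All loss before post-intervention: v = (1 − ρ²)/0.75 + (1 − ρ)² = 1 + 0.25 = 1.25.
- All loss after it: the residual variance of the 3-month score given both earlier scores is 2/3, so v = (2/3)/0.75 + 1/3 = 1.222.

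*Baseline-adjusted, or equal baseline means*
- All loss before: v = (1 − ρ²)/0.75 = 1.
- All loss after: v = (2/3)/0.75 + (1/9)(0.75) = 0.972.

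| Contrast | v | SE at 75 per arm | Power at N = 150 | N for 80% (4kv/d²) |
|---|---|---|---|---|
| Unadjusted, early loss | 1.25 | 0.183 | 78.2% | 157.0 → 158 |
| Unadjusted, late loss | 1.222 | 0.181 | 79.1% | 153.5 → 154 |
| Adjusted, early loss | 1 | 0.163 | 86.5% | 125.6 → 126 |
| Adjusted, late loss | 0.972 | 0.161 | 87.4% | 122.1 → 124 |

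Splitting the loss evenly gives 78.7% (156 needed) and 87.0% (124 needed). Adjusting the completers' 3-month score, rounded up to 48 per arm before inflation, gives 96/0.75 = 128. The unadjusted model at 150 detects d of 2.802 × SE, which is 0.506 to 0.511.

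**3. What 112 would deliver**

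With 56 per arm and the same v: unadjusted SE is 0.211 to 0.209, power 66–67%; adjusted SE is 0.189 to 0.186, power 75–77%.

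**The case against.** The strongest reply is that 150 is a sensible number whatever the paragraph says. That stands. The unadjusted mixed model falls short of 80% by only one or two points, well inside the uncertainty of an assumed ρ and dropout rate. With late dropout it needs 154, within 3% of 150. If baseline K10 is adjusted for, as Data analyses partly suggests, 150 is more than enough.

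Three stronger readings are tempting, and the documents do not support them.

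- *The trial is underpowered.* This holds only for the unadjusted contrast, and there only slightly. A figure of about 75% can be obtained from completers' change scores (62.79/0.75 per arm, 168 in total for 80%), but the trial plans intention-to-treat mixed models that keep partial data, so that figure is not the power of the planned analysis.
- *The trial was powered at 90% and the paragraph misprints it.* The match at 90% is close, but the article never mentions 90% or says that the average version was used. Other departures from the stated inputs also come near 150: the average version at 80% power gives 147 with ρ = 0.8. The mismatch does not depend on how it arose.
- *Baseline adjustment is already planned, so nothing needs changing.* The wording ties adjustment to differences found on examining the groups. That does not commit the analysis to adjustment, so it cannot carry the higher power figure.

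It is also fair that the formula version and sidedness are details an article may leave out. That excuses silence on them; it does not excuse a result that the stated inputs fail to give under the versions tried.

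**Conclusion.** The point holds in limited form. The statement that 150 is the minimum for 80% power does not follow from the inputs: the average version of the cited calculation gives 112, and the slope version 164 to 168 (154 to 157 with the N × 1.25 shortcut). The paragraph also does not say which contrast it powers, and the one version found to give 150, the average at 90% power, counts baseline as an outcome.

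For the primary outcome, 150 gives about 78–79% power unadjusted (154 to 158 needed for 80%) and about 86–87% adjusted (124 to 128 needed). The planned total is therefore roughly adequate; the derivation and the stated power are what is wrong. Severity is moderate. The results rest on a two-sided test, compound symmetry with ρ = 0.5, equal SDs, and 25% missing at random at 3 months. At ρ = 0.5 the SD of the change, √[2(1 − 0.5)] = 1, equals the single-visit SD, so it does not matter which of the two d is standardised by.

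**What to change.** Rewrite the sample size paragraph for the between-group difference in K10 change from baseline to 3 months, stating the formula version, the sidedness and the dropout assumption. In Data analyses, replace the adjustment that depends on observed baseline differences with unconditional adjustment for baseline K10 (or a model with equal baseline means). Then report that 150 participants with 25% missing at 3 months give about 86–87% power for d = 0.5, and that about 124 to 128 would give 80%. If the unadjusted model is kept, state about 78–79% instead.

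The cost is a reworded paragraph and one sentence on the model. It needs no extra participants and no change to visits or randomisation.
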